## 8.4 Decision Criteria

The decision to progress from Phase 1b to Phase 2a will be based on the number of severe skin reactions reported, with guidance and recommendations from the trial DMC, as reported in the statistics section of the trial protocol and trial master file.

Decision criteria at the end of Phase 2a are predominantly based on the response rate and critical number of responses observed in the treatment group, according to the Fleming A’Hern design. Tumours receiving placebo treatment are not expected to respond to treatment. Using Fleming A’Herns early phase methodology (Fleming 1982, Ahern 2001) any response on the experimental treatment <5% would not indicate a treatment worthy of further investigation. The justification to investigate CT327 further is based on observing a minimum number of responses referred to as the critical number as specified in the document entitled “Critical Number” which is located in the Statistical Trial Master File.

The benchmark for the definition of ‘response’ was set as 30% reduction in tumour volume given the WHO RECIST oncology criteria. As specified in the protocol, consideration will be given to shifts in this criteria, to smaller reductions in volume, to observe the impact on the response rate and Fleming A’Hern critical number in the treatment group, as outlined in 8.3 above. The reasoning for this exploratory analyses in this early phase clinical trial is to allow further investigation of a biologically interesting treatment which may have not hit a statistical boundary. The conclusions from the trial will be discussed with the DMC and reported with their independent guidance and recommendations.

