#### **2.1.2 Cohort 2**

All tumours will contribute to the analysis based on the total number randomised (intention to treat population). A secondary analysis will be reported based on the number of tumours which have been treated for 12 weeks (per protocol population).

The primary outcome measure is the number of tumours responding to treatment by 12 weeks reported as a proportion of the number of tumours randomised in the actively and placebo groups separately.

According to WHO-RECIST criteria, a reduction in 30% volume would be sufficient to classify a 'response' to treatment in oncology. In this trial we will use this criteria as a bench mark when determining a response in this patient population. As such one of the outcomes will be to consider and confirm a definition of 'response' to treatment in this group of patients. Tumour volume will be measured on 8 - 10 predetermined identified tumours in each patient prior to randomisation (baseline) and measured again on the same tumours at 4 and 12 weeks. The change in volume for each tumour will be recorded and classified as either having a response to treatment or not.

As an early phase trial, statistical analysis will be exploratory (not based on hypothesis testing) and will be based on descriptive data presented by treatment group. Continuous measurements (including change in tumour volume from baseline) will be summarised and reported as medians and ranges (inter-quartile ranges). Categorical data (including proportions of tumours with adverse events and outcomes from the Pain Assessment Forms) will be summarised and reported as percentages and confidence intervals (95%). Since multiple tumours are sited in individual patients, a secondary analysis based on a multi-level

modelling approach will be undertaken to investigate the relationship between any change in volume and randomised treatment accounting for the multi-level nature of the tumour measurements.

QoL tools (EQ5D, DLQ) will be scored according to scoring manuals and actual scores will be reported descriptively.

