### **Cohort 2**

It is anticipated that 75 tumours could be measured in each treatment arm (150 tumours in total). Tumours receiving placebo treatment are not expected to respond to treatment, set to be very small at 5% ( $p_0$ ). This is the first exploratory trial and as such the design parameters are provided as an exemplar of the size of errors that may be anticipated with these patient numbers.

Using Fleming A'Herns early phase methodology (Fleming 1982, Ahern, 2001) any response on the experimental treatment  $<5\%$  ( $p_0$ ) would not indicate a treatment worthy of further investigation. 75 tumours recruited in the experimental arm would provide evidence of a minimum level of efficacy of approximately 15% ( $p_1$ ), indicating that a level of efficacy of  $>15\%$  would warrant further investigation, with associated error levels of 3.4% type I error ( $\alpha$ ) and 10.8% type II error ( $\beta$ ). This level of efficacy seems clinically plausible and relevant given that there is no current treatment in use for these patients.

The justification to investigate CT327 further is based on observing a minimum number of responses, referred to as the critical number (specified in the Statistical Analysis Plan). The trial will recruit an equal number of placebo-treated tumours to provide an unbiased benchmark.

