### **Cohort 2**

The Fleming A'Hern design would indicate no further investigation is warranted if the observed number of clinical responses is less than the critical number (as specified in the Statistical Analysis Plan).

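### The Phase 2a critical-number rule has no placebo term, so its 3.4% type I error holds only if background response is 5% or less

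*Combined protocol and SAP*

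**What the plan says.** **Rule.** SAP 8.4 says the decision is "predominantly based on the response rate and critical number of responses observed in the treatment group", following Fleming-A'Hern. Protocol 14.3 states it from the other side: "no further investigation is warranted if the observed number of clinical responses is less than the critical number". The number itself is kept in a separate file that is not part of these documents.

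**Assumed background.** Protocol 14.2: "Tumours receiving placebo treatment are not expected to respond to treatment, set to be very small at 5"%. Neither document cites natural-history, vehicle-response or measurement-error data for that figure.

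**Design figures.** Protocol 14.2: "75 tumours recruited in the experimental arm would provide evidence of a minimum level of efficacy of approximately 15"%, "with associated error levels of 3.4% type I error" and "10.8% type II error".

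**Role of placebo.** Protocol 14.2: "The trial will recruit an equal number of placebo-treated tumours to provide an unbiased benchmark". Protocol 14.1 (Cohort 2) has responses "reported as a proportion of the number of tumours randomised in the actively and placebo groups separately". SAP 8.2.2.2 and the response table in SAP Appendix 3 do the same, with a 95% CI for each arm. SAP 8.2.2.3 adds multilevel models of tumour volume with randomised treatment as a covariate.

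**Response cut-off.** SAP 8.4 provides for considering smaller volume reductions than 30% and their effect on the response rate and critical number in the treatment group, so that an interesting treatment that missed the boundary can still be pursued. SAP Appendix 4 tabulates cut-offs from 20% to 40% without separate columns for active and placebo.

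**The concern.** The primary objective is whether tumours respond to CT327. A count of responders on active answers that only if the response rate without drug is known. The trial randomises sides within patients and measures the same endpoint on placebo-treated tumours, so it will estimate that rate directly. The written rule uses the assumed 5% instead.

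If vehicle effect, spontaneous change or measurement error produces responses in more than 5% of tumours, the rule credits them to the drug. The stated type I error then no longer describes the chance of taking an inactive ointment forward. Relaxing the 30% cut-off while looking only at the treatment group sharpens the problem, because an easier cut-off can only keep or raise the background rate, and the 5% was set with the 30% definition in view.

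**Working it through.** **Inputs (protocol 14.2).** n = 75 active tumours, p0 = 0.05, p1 = 0.15, type I error 3.4%, type II error 10.8%. Tumours are treated as independent, as the stated design does.

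**1. Reproduce the plan's figures.** For critical number r and X ~ Bin(75, p), type I error = P(X ≥ r | 0.05) and type II error = P(X < r | 0.15).

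| r | Type I | Type II |
|---|---|---|
| 7 | 8.1% | 5.4% |
| **8** | **3.4%** | **10.8%** |
| 9 | 1.2% | 18.9% |

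Only r = 8 matches both printed errors, so 8 of 75 (10.7%) is taken as the critical number.

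**2. Chance that an inactive ointment reaches 8 of 75.** Set the active rate equal to the background rate p and compute P(X ≥ 8 | p). Values of p above 5% are assumptions.

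| Background p | P(X ≥ 8) |
|---|---|
| 5% | 3.4% |
| 6% | 8.0% |
| 8% | 25.0% |
| 10% | 47.9% |
| 12% | 69.1% |
| 15% | 89.2% |

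**3. Clustering.** Assume 15 patients with 5 active tumours each and a beta-binomial intra-patient correlation of 0.1 to 0.3. At a 5% background the error is then 6.1% to 10.3% rather than 3.4%. At 10% it is 46% to 47%, and at 15% it is 78% to 85%. The steep rise with background remains.

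**4. Relaxing the cut-off (illustration).** Assume log-normal error with a 15% CV for a visit's mean volume and no true change. The false-response probability for a cut-off of c% is Φ(ln(1 − c/100) / (√2 × 0.15)).

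- 30% cut-off: Φ(ln 0.7 / 0.212) = 4.6%, giving P(X ≥ 8) = 2%.
- 20% cut-off: Φ(ln 0.8 / 0.212) = 14.6%, giving P(X ≥ 8) = 88%.

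The CV is an assumption. The illustration shows that a 5% background can be right for one cut-off and wrong for another.

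**5. What a margin over placebo would do.** As one example, require at least 8 responders on active and at least 4 more than on placebo, with 75 tumours per arm.

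| Active / placebo rate | Active-only rule | With margin |
|---|---|---|
| 10% / 10% | 48% | 16% |
| 15% / 15% | 89% | 21% |
| 20% / 20% | 99% | 24% |
| 15% / 5% | 89% | 83% |
| 15% / 8% | 89% | 66% |
| 15% / 10% | 89% | 52% |

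The first three rows are false-go probabilities and the last three are power. A stricter version replaces the margin with a one-sided 5% pooled z-test and keeps the critical number. It holds false go at about 5% or below for backgrounds from 5% to 20%, but power at 15% versus 5% falls to 66%.

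**The case against.** The plan declares itself exploratory and not based on hypothesis testing. Protocol 14.2 offers the error rates as an exemplar, and a wrong go leads to further study, not to a confirmatory claim. That stands, and it lowers the severity. It does not remove the point, because a decision rule with stated errors is still pre-specified.

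Three stronger readings are tempting, and the documents do not support them.

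- *An inactive ointment passes whenever background response exceeds 5%.* It does not. The probability is 8% at a 6% background and still just under one half at 10%. What is lost above 5% is the 3.4% guarantee.
- *The placebo side is never used, or cannot change the decision.* Placebo response is reported beside active with a CI, and SAP 8.2.2.3 models volume by treatment. SAP 8.4 says *predominantly* and provides for DMC discussion. Protocol 14.3 states only when to stop, so the critical number can be read as a floor. The file holding the number has not been seen. What is missing is a planned between-arm difference in response and a stated link to the decision.
- *Background response is in fact above 5%.* Nothing in the documents shows this. Protocol 13.2 describes the imaging system as validated and reproducible, though without a figure, and SAP 8.1.2 averages three readings per visit. At the 15% CV assumed above, false response at the 30% cut-off is 4.6%, which agrees with the plan's 5%.

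**Conclusion.** The point holds in this form: the quantitative rule depends on an unsupported 5% that the trial itself will measure on placebo but does not feed into the rule. If the true background is 5% or less and tumours are independent, the stated error stands. At an 8% background the chance that an inactive ointment reaches the critical number is 25%, at 10% it is 48%, and at 15% it is 89%.

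These figures rest on an inferred critical number of 8 of 75, on illustrative background rates and on independence between tumours. Informal use of the placebo result remains possible under SAP 8.4, but discretion exercised once results are known is not a pre-specified criterion. Should-fix.

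**What to change.** - **SAP 8.2.2.2:** add the within-patient active-minus-placebo difference in 12-week response, with a confidence interval that respects clustering by patient.
- **SAP Appendix 4:** show each alternative cut-off separately for active and placebo.
- **SAP 8.4 and protocol 14.3:** state that reaching the critical number is necessary but not sufficient, that it is read together with the between-arm difference (including at any relaxed cut-off), and that the 3.4% error is conditional on a 5% background.

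No particular numerical margin over placebo is recommended here. If the sponsor wants one, it should choose it openly and show its operating characteristics. The example of at least 4 more responders is a trade-off: false go stays at 21% to 24% for backgrounds of 15% to 20%, and power for a 15% active rate depends heavily on the placebo rate.

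**Cost:** SAP wording, a short protocol edit and a little extra analysis. No new patients, visits or measurements are needed. A go decision becomes somewhat harder to reach. The change should be made before unblinding.

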## 8.3 Additional Analyses

According to the WHO-RECIST criteria, a 30% reduction in volume is sufficient to classify a “response” to treatment in oncology. In this trial we use this criteria as a bench mark when determining a response in this patient population. As such a further outcome is to consider and confirm a definition of “response” to treatment in this group of patients. We will consider how many tumours are responders, stable or progressive disease at different levels of “partial response”. We will report the number of tumours who would be classified as responders for lower levels of reduction in tumour volume at both 4 weeks and 12 weeks. Response rates in the trial set will be presented in tabular form for alternative definitions, based on -5% and - 10% changes in the RECIST definition (Appendix 4).

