### Additional Analysis

| Reduction in tumour volume | Complete Response | Partial Response | TOTAL RESPONSE | Stable Disease | Disease Progression | Not applicable | Total |
|----------------------------|-------------------|------------------|----------------|----------------|---------------------|----------------|-------|
| ≥ 20%                      | N (%)             |                  |                |                |                     |                |       |
| ≥ 25%                      |                   |                  |                |                |                     |                |       |
| ≥ 30% (RECIST)             |                   |                  |                |                |                     |                |       |
| ≥ 35%                      |                   |                  |                |                |                     |                |       |
| ≥ 40%                      |                   |                  |                |                |                     |                |       |

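### SAP 8.4 offers lower response cut-offs as a way forward after a missed boundary, contrary to protocol 14.3 and with no matching null rate or critical number

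*Combined protocol and SAP*

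**What the plan says.** Protocol 14.2 (Cohort 2) sizes the active side at 75 tumours with a null rate of 5% and a target of 15%, "with associated error levels of 3.4% type I error" and "10.8% type II error". Protocol 14.1 and SAP 8.1.2 use a 30% volume reduction as the benchmark for response. Protocol 14.3 says no further investigation is warranted if responses are fewer than the critical number. SAP 8.4 places that number in a separate file that is not part of the documents.

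Under the title Decision Criteria, SAP 8.4 says the decision rests predominantly on the critical number. It then says "consideration will be given to shifts in this criteria, to smaller reductions in volume, to observe the impact on the response rate" and on the critical number in the treatment group. The stated reason is "to allow further investigation of a biologically interesting treatment which may have not hit a statistical boundary". The section calls this exploratory and sends the conclusions to the DMC.

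SAP 8.3 supplies the detail: "We will report the number of tumours who would be classified as responders for lower levels of reduction in tumour volume", at both week 4 and week 12, with shifts of 5 and 10 percentage points. The Appendix 4 shell has rows from 20% to 40% under "Reduction in tumour volume", but no active/placebo columns and no time-point label. The response table in Appendix 3 does separate active from placebo.

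**The concern.** The 5% null rate and the 3.4% error belong to the 30% definition. Every tumour that shrinks by 30% has also shrunk by 25% and by 20%. Lowering the cut-off therefore cannot reduce the no-effect response rate, and with any measurement noise or natural fluctuation it raises it. A critical number set for 5% does not hold the stated error at a cut-off where the no-effect rate is 8% or 15%.

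Reporting several cut-offs is legitimate, since confirming the response definition is a listed secondary outcome. The difficulty is that SAP 8.4 gives the lower cut-offs a decision purpose, to be used when the boundary has been missed, and looks at them in the treatment group. The same section says the protocol specifies this. The protocol supplied (version 3.0; the SAP cites V2.1) speaks only of considering and confirming a definition of response. It does not connect other cut-offs to the critical number. At stake is the meaning of the trial's only efficacy decision rule.

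**Working it through.** **Inputs from the documents.** n = 75 active tumours, null rate 5%, target 15%, errors 3.4% and 10.8% (protocol 14.2); cut-off 30% (SAP 8.4); lower cut-offs 25% and 20% (SAP 8.3 and Appendix 4).

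**1. Reproduce the plan's figures and recover the critical number.** Exact binomial, with type I error = P(X ≥ r | 75, 0.05) and type II error = P(X < r | 75, 0.15):

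| r | type I | type II |
|---|---|---|
| 7 | 8.10% | 5.44% |
| 8 | 3.36% | 10.82% |
| 9 | 1.24% | 18.89% |

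Only r = 8 matches 3.4% and 10.8%.

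**2. Effect of keeping 8, by no-effect rate alone.** P(X ≥ 8 | 75, p): p = 7% gives 15%; 8% gives 25%; 10% gives 48%; 12% gives 69%; 15% gives 89%.

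**3. What p might be at 25% and 20%.** The documents do not say, so this needs an assumption. Anchor each model so that exactly 5% of no-effect tumours fall by at least 30%, then read off the rate at cut-off c.

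- Log-normal volume ratio with log-drift μ: σ = (−ln 0.70 + μ)/1.645 and p = Φ((ln(1−c) − μ)/σ). With μ = 0, σ = 0.3567/1.645 = 0.217; p = Φ(ln 0.75/0.217) = 9.2% and Φ(ln 0.80/0.217) = 15.2%.
- Normal percentage change with mean m: SD = (0.30 + m)/1.645 and p = Φ((−c − m)/SD).
- Student t, centred at 0: scale = 0.30/t(0.95, df).

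| No-effect model | p at 25% | P(≥8) | p at 20% | P(≥8) |
|---|---|---|---|---|
| Log-normal, no drift | 9.2% | 39% | 15.2% | 90% |
| Log-normal, log-drift −0.05 | 10.1% | 49% | 17.7% | 97% |
| Normal, mean 0 | 8.5% | 31% | 13.6% | 82% |
| Normal, mean growth 5% | 7.9% | 24% | 12.0% | 69% |
| Normal, mean growth 10% | 7.5% | 20% | 10.9% | 58% |
| t, 5 df | 7.7% | 22% | 11.8% | 68% |
| t, 3 df | 7.2% | 17% | 10.7% | 56% |

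**4. Vary the anchor.** Log-normal, no drift, with the true no-effect rate at 30% set lower:

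| Rate at 30% | P(≥8) at 25% | P(≥8) at 20% |
|---|---|---|
| 1% | 0.2% | 18% |
| 2% | 3% | 47% |
| 3% | 11% | 69% |
| 5% | 39% | 90% |

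**5. If the number were re-derived.** The smallest r with P(X ≥ r) ≤ 5% under the log-normal, no-drift model is 12 at the 25% cut-off (error 4.2%) and 18 at the 20% cut-off (error 3.0%). Under the t model with 3 df it is 10 (4.3%) and 14 (2.8%).

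**6. Independence.** All of this treats tumours as independent, as the stated design does. With 15 patients of 5 active tumours and an intraclass correlation of 0.1 (beta-binomial simulation), P(≥8) at a 5% rate is about 6% rather than 3.4%.

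**The case against.** Much of the case on the other side stands.

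- A reader might infer that the SAP keeps 8 while lowering the cut-off. It does not say so. Observing the impact on the critical number can equally mean re-deriving it, and the file that holds the number is not available. This is a gap, not a stated rule.
- A reader might take 39% and 90% as the error of the plan. They come from one model, log-normal with no drift and a 5% anchor. That 5% is a design setting; the protocol does not expect placebo tumours to respond. Volume is the mean of three readings on a system the protocol describes as sensitive and reproducible, so the true no-effect rate may be lower. At 1-2%, the 25% cut-off stays within the stated 3.4%.
- A reader might call these figures a false-go risk. They are the chance that the count reaches 8. The decision is predominantly, not solely, based on that count; the DMC advises; and a go means further investigation.
- It would also go too far to say that the stated type I error has no meaning. Protocol 14.2 offers the errors as an exemplar, and protocol 14.1 rules out hypothesis testing.
- The cut-offs are not an open choice after the data. The grid is pre-specified and includes stricter rows at 35% and 40%.
- Placebo behaviour is not hidden altogether. Protocol 14.1 promises descriptive data by treatment group, and SAP 8.2.2.1 reports percentage volume change by randomised group. The missing columns are in one table shell.

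None of this removes the conflict with protocol 14.3. The exploratory label sits beside a stated decision purpose, and the shell laid out for judging the cut-offs does not show placebo at the same cut-off.

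**Conclusion.** The point holds as a conflict and a gap in the decision rule. SAP 8.4 opens a second route to further investigation after a missed boundary, protocol 14.3 closes it, and no null rate or critical number accompanies the lower cut-offs.

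The size is conditional. With 8 of 75 kept, independent tumours and a 5% no-effect rate at 30%, the chance of reaching the number rises at least about five-fold in every model tried (17.4/3.36 = 5.2 at the low end). With a 1-2% rate under the log-normal model, the 25% cut-off does little harm against the stated 3.4%, but the 20% cut-off still gives 18-47%. If the number is properly re-derived for each cut-off, the inflation at each single cut-off disappears. The SAP needs to say which is meant.

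**What to change.** - **SAP 8.4:** state that the critical-number decision uses only the 30% definition at week 12, and delete the sentence giving the rescue purpose. Alternatively, pre-specify a null rate and a critical number for each lower cut-off, with the basis for each.
- **SAP 8.3 and Appendix 4:** split every row by active and placebo and by week 4 and week 12, and label the table hypothesis-generating.

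Selecting a new cut-off from the placebo distribution is not part of this fix. At a 5% limit it would rest on at most 3 of 75 tumours (0.05 × 75 = 3.75), and it too would be chosen after seeing data.

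The cost is SAP wording and one table shell, with no new data. The sponsor gives up an informal second route to a go decision. The change should be made before the phase 2a data are unblinded.
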